### Study conditions

A) Intensified adapted DBT program plus six months standard outpatient DBT

Twelve-week inpatient DBT was developed in the Jelgersma Center for Personality Disorders. This treatment unit provides accommodation for nine patients. Patients are admitted five days a week. Staff is only present in the daytime. During the weekends the patients stay at home. The therapy [16] consists of DBT skills training [25], individual psychotherapy (45 minutes a week during the inpatient and the outpatient program), crisis consultation if needed, and weekly meetings of the consultation team for all trainers and therapists for one hour. Staff also receives supervision twice-weekly.

Individual psychotherapy takes place on a weekly basis. The order of the topics of each session is based on Linehan’s protocol [16], and is pre-determined: suicidal and self-destructive behavior, therapy-interfering behavior, quality of life-interfering behavior and generalization of the skills taught in the training. Each therapy session starts by filling out diary cards that hold all the information concerning the problematic behaviors, which are the primary goal of the treatment, but also behaviors that influence the primary goals (such as alcohol and drug use, the urge to self-harm, substance abuse, dissociation, level of applied skills). Skills’ training takes place during the inpatient program on a weekly basis, but discussion of theory and homework classes are separated in time throughout the week (in total two and a half hours). The skills taught are standard DBT skills and combine self-regulation and change skills, and skills for self-acceptance and acceptance of others: Core mindfulness skills, Interpersonal effectiveness skills, Emotion regulation skills, Crises skills and Radical acceptance. Missed meetings need to be caught up by watching the video recordings that are made of all the trainings sessions.

Patients also receive daily mindfulness classes, two hours of drama therapy, psycho-educational classes about sexuality, substance abuse and medication, and the possibility of getting help in applying principles of validation and behavioral analysis skills. Other program parts are mainly based on living in a group, such as house-keeping meetings. In order to facilitate skills generalization, patients and staff developed psycho-educational evening sessions (two) in which information on BPD and DBT is given, followed by a training program (six sessions) in which patients together with family and friends can get help in applying skills. Each session lasts two hours. The first two sessions are spent on psycho-education about BPD, DBT and the content of the treatment program. In the next four sessions, all participants are asked to commit to practice the skills that are taught in the program with each other.

During evening and night hours, no staff is present. The results from the data gathered during the developmental phase of the program (October 2009 to September 2011), show that this does not lead to an increase in difficulties in handling relationships.

B) Standard outpatient DBT for 12 months

Patients assigned to standard dialectical behavior therapy receive 12 months of treatment as specified in the DBT manual [16] in one of the three participating regional psychiatric centers of Rivierduinen. The treatment is according to protocol and combines weekly individual cognitive-behavioral psychotherapy sessions with the primary therapist (45 minutes a week, weekly skills-training groups lasting two and a half hours per session (135 minutes), and if needed, consultation and weekly consultation meetings for trainers and therapists (one hour). Individual therapy, in both in- and outpatient programs, focuses primarily on motivational issues, including the motivation to stay alive and to stay in treatment. Group skills training [25] teaches Core Mindfulness skills, Interpersonal effectiveness skills, Emotion regulation skills, Crises skills and Radical acceptance.

### Selection of the therapists

Extensive attention was given to the selection of the therapists. Therapists and skills trainers per condition need to meet the highest quality requirements of good training, experience and supervision. All therapists/trainers are psychologists/psychiatrists, or registered nurses/social workers (n = 30). All have received at least a three-day introductory training in DBT principles administered by Dialexis, the training institute of the Dutch DBT association. Supervision will be given by the main researcher ([name]), who is head of the Dutch DBT association and has received extensive training from [name] in Seattle, USA. The treatment integrity in DBT is protected by systematic evaluation of video recorded individual and skill training sessions, by trained adherence coders.

### Objectives

The primary objective is to investigate whether this program is more effective in declining the proportion of patients that show parasuicidal behavior in the first three months of treatment, compared to standard outpatient DBT. We expect that after 12 weeks of inpatient DBT treatment, 20% of the patients will still show suicidal/self-harming behavior (measured by Life Time Parasuicide Count and items of the Borderline Personality Disorder Severity Index) compared to 60% of the patients in standard outpatient DBT. We expect this difference to be sustained after 24 weeks, though it may be reduced between 24 and 52 weeks.

The secondary objectives are: (i) to investigate whether short-term inpatient DBT is more effective in reducing other general (borderline) symptoms, (ii) to investigate whether short-term inpatient DBT is more effective in increasing quality of life, and (iii) to assess the cost-effectiveness of short-term inpatient DBT compared to outpatient DBT in terms of costs per reduced suicide attempts/self-destructive acts and cost per Quality Adjusted Life Year (QALY) from a societal perspective. We expect (i) a stronger decline in Borderline Personality Disorder Severity Index- and Brief Symptomatology Inventory scores and (ii) a stronger increase in quality of life (SF-36 and EQ-5D)-scores in the first three months of inpatient DBT as compared to the control group. We anticipate this difference to be sustained after 24 weeks, though it may reduce between 24 and 52 weeks. We also expect (iii) the initial higher cost of the intensive intervention will lead to better effects and possibly even lower cost than the control condition. Cost savings may be generated in the long run (after one year).

### Measurements

#### Screening

Vragenlijst voor Kenmerken van de Persoonlijkheid (VKP) [26], a paper-and-pencil self-report questionnaire that measures personality disorders as defined in the DSM-III-R [27] and the *International Classification of Diseases, version 10* (, ) [28], was used as a screening test. Next to a categorical diagnosis (‘negative’, ‘probable’ and ‘positive’), it yields a dimensional score for each disorder. Reliability and validity have proven to reasonable [29].

#### Axis I and axis II disorders

For inclusion, patients had to meet the criteria for borderline personality disorder, as measured by the Dutch translation of the *Structured Clinical Interview for DSM-IV, version II* (SCID-II) [30,31]. The SCID-II is a clinician-rated semi-structured clinical interview developed to measure the ten DSM-IV axis II personality disorders, supplemented by the depressive and the passive-aggressive personality disorder [32]. This instrument has shown adequate interrater and internal consistency reliability [33].

The web-based Dutch version of the *Mini International Neuropsychiatric Interview* (MINI-PLUS) [34,35] was used to assess exclusion criteria. The MINI-PLUS is a structured clinician-rated diagnostic interview that is used to determine the most common DSM-IV [32] and ICD-10 psychiatric disorders [28]. Reliability and validity are considered good [34,36].

The interviewers who conducted the SCID-II and MINI-PLUS interviews had a master’s degree in psychology. They received training in how to carry out the interviews and were supervised by an experienced clinical psychologist. The interviewers had the opportunity to verify their diagnosis with a psychiatrist.

### Outcomes

*Frequency of suicide attempts/self-harming acts*, as measured by the *Lifetime Parasuicide Count* (LPC: [37]. The LPC is a sixteen-item clinician-rated interview that determines parasuicide markers (date, method, intent, and medical treatment) of respectively the first, most recent and most severe parasuicide, and determines the frequency and subsequent medical treatment of 12 methods of self-mutilating behaviors (for example, cutting, burning and pricking). Data on the psychometric properties of this instrument were not available.

The *Borderline Personality Disorder Severity Index* (BPDSI) [38] is a clinician-rated semi-structured interview assessing the frequency of borderline symptoms in the previous three-month period. The BPDSI-IV has shown high interrater reliability, moderate to high internal consistencies and very good discriminant, concurrent and construct validity [38,39]. The BPDSI-IV has been used in various trials and proved to be sensitive to change among others. [40,41]. Patients have reported that during the interview they feel their problems are acknowledged [42].

The *SF-36*[43], or *Medical Outcomes Study 36-Item Short Form Health Survey*, is a short-form, self-report health survey with 36 questions. It yields an eight-scale profile of functional health and well-being: Physical Functioning, Role-Physical, Bodily Pain, General Health, Vitality, Social Functioning, Role-Emotional and Mental Health as well as psychometrically-based physical and mental health summary measures and a preference-based health utility index. A higher score indicates a better state of health [43]. A Dutch version was translated and validated by Aaronson *et al*. [44]. Data from the SF-36 were collected using a computer-based version, *SF-6D.*

*SF-6D.* The Sheffield Health Economic Group derived a preference-based measure of health from the SF-36 [45]. The new preference-based measure, known as the SF-6D, is derived from 11 items of the SF-36 and is composed of six dimensions of health with four to six levels each.

The *EQ-5D*[46], or *EuroQol 5 Dimensions* descriptive system, is a paper-and-pencil self-report questionnaire that consists of five dimensions (Mobility, Self Care, Usual Activities, Pain/Discomfort and Anxiety/Depression) with three levels each (no problems, some problems and extreme problems), thus defining 243 distinct health states. Each of these health states can be assigned a particular utility using a scoring algorithm. The Dutch tariffs were determined in a time trade-off study. EQ-5D utilities range from −0.329 to 1. Assessment takes one to two minutes.

The *TiC-P* or ‘*Trimbos and iMTA Questionnaire on Costs Associated with Psychiatric Illness*’ (TiC-P) [47] is a validated tool commonly applied in economic evaluations of treatments in mental health care. The TiC-p is a paper-and-pencil self-report questionnaire that consists of two parts. The first part measures direct medical costs. The second part estimates the productivity costs. It includes a short form of the Health and Labor questionnaire (HLQ), consisting of three modules that measure productivity losses: absence from work, reduced efficiency at work and difficulties with job performance [48]. The TIC-P is considered to be a feasible and reliable instrument for collecting data on medical consumption and productivity losses in patients with mental health problems. The construct validity of questions related to contacts with psychotherapist and long-term absence from work is satisfactory [49].

The BSI, or *Brief Symptomatology Inventory* (BSI) [50], is a self-report questionnaire that includes 49 items grouped into nine scales that encompass nine primary dimensions of psychopathological symptoms: psychoticism, somatization, depression, hostility, phobic anxiety, obsessive-compulsivity, anxiety (panic), paranoid ideation, and nervous tension. Derogatis and Melisaratos [50] presented appropriate coefficients of internal consistency of the BSI ranging from 0.71 to 0.85, test-retest reliability coefficients ranging from 0.68 to 0.91, and evidence for the a good construct validity of the BSI. Other studies have reported similar estimates, for example, see references [51,52]. Data of the BSI were collected using a computer-based version.

### Sample size

We expect that after 12 weeks, 20% of the patients of the intervention group will still show suicidal and/or self-harming behavior compared to 60% of the patients in the control condition. To be able to detect a difference of 40% after 12 weeks, with a power of 0.80 and an α = 0.05, a minimum of 23 patients per experimental condition is required. We will randomize between approximately 70 patients during the study period to guarantee enough power, taking into account an expected 30% drop-out rate.

### Randomization

#### Sequence generation

Treatment allocation is carried out by a computer program, developed by the Amsterdam Medical Center. To increase the likelihood of comparable treatment groups, a minimization method is preferred. To preserve the random character of allocation, a biased coin procedure will be used. In case of imbalance, the allocation probability is modified from 50/50 to 80/20. Minimization variables are: level of severity of borderline symptomatology (BPDSI score ≥ 40), level of suicidality/self-harming behavior (LPC score ≥ 14), and age.

#### Allocation concealment

The sequence was concealed until interventions were assigned.

### Implementation

When patients register in the participating psychiatric centers, crisis team members or staff members working at the front office decide whether or not this patient is a candidate for DBT, based on a rapid assessment of BPD symptomatology. Patients are informed about the central recruitment and diagnostic facility and are given the phone numbers of the project leader and coordinator. After a short, standardized telephone interview with the project leader or the coordinator, in which general information on the interventions and study is given, patients need to fill out a screening instrument (Vragenlijst Kenmerken Persoonlijkheid, VKP) [26] and send it back to the central diagnostic facility. Subsequently, a psychologist contacts the patient for a briefing of the results. If the screening instrument indicates that presence of BPD is probable, then psychologist and patient make an appointment for a thorough examination within three weeks. During this thorough examination, with use of the MINI-PLUS and SCID-II, presence of DSM axis I and axis II disorders are verified. Frequency of borderline complaints and parasuicidal gestures are assessed using respectively BPDSI and LPC. All assessment tools employed have demonstrated reliability and validity (described in detail below). Informed consent is discussed and signed. After signing the informed consent, patients are randomized and the diagnostician reports the allocation of the treatment back to the patients. The allocated treatment center then contacts the patient and starts treatment.

### Blinding

No blinding took place.

### Statistical analysis

All participants who are randomised will be included in the comparison and analyzed according to their randomized allocation (intent-to-treat analysis). Wherever possible, we will continue to collect follow-up data from participants after they drop out of treatment, so that the dataset will be as complete as possible. All analyses will be carried out using SPSS (Statistical Package for the Social Sciences) 19 [53]. The effect of the intervention in terms of proportion of respondents still showing suicidal and/or self-destructive behavior after 12 weeks, and the retention of this effect between 24, 36 and 52 weeks, will be computed with the help of longitudinal logistic regression, with time, experimental condition and their interaction as independent variables. The effect of the intervention in terms of reduction in mean BPDSI, LPC, SF-36, and the BSI ratings over time, will be computed with the help of a mixed model linear regression analysis with time, experimental condition and their interaction as independent variables. Missing values will be taken into account by using full information maximum likelihood method estimation. Since there may be some heterogeneity in the implementation of standard DBT across the three different regional centers, between-center heterogeneity will be explored in subgroup analyses.

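### Allocation is minimised on BPDSI, LPC and age, but the outcome models leave all three out, which makes the primary test conservative and costs power

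*Protocol article*

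**What the plan says.** - **Allocation.** Under Randomization, Sequence generation, the article describes minimisation with a biased coin that moves from 50/50 to 80/20 when the arms are out of balance. "Minimization variables are: level of severity of borderline symptomatology" (BPDSI score of 40 or more), then LPC score of 14 or more, and age.
- **Primary model.** Under Statistical analysis, the effect on the proportion with the behaviour at week 12, and how far it is retained at weeks 24, 36 and 52, "will be computed with the help of longitudinal logistic regression, with time, experimental condition and their interaction as independent variables". The linear mixed models for mean BPDSI, LPC, SF-36 and BSI have the same three terms.
- **Outcome instruments.** Objectives says the primary behaviour is measured by the LPC and by BPDSI items. Two of the three minimisation factors are therefore the same instruments at baseline.
- **Sample size.** The calculation is for one visit: "To be able to detect a difference of 40% after 12 weeks", "with a power of 0.80 and an α = 0.05", with 20% expected in the intervention arm "compared to 60% of the patients in the control condition". This gives 23 per arm, and about 70 randomised to allow for 30% drop-out.
- **Expected course.** Objectives adds: "We expect this difference to be sustained after 24 weeks, though it may be reduced between 24 and 52 weeks".

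**The concern.** Minimisation removes chance imbalance on its factors, so the arm difference varies less from trial to trial than under simple randomisation. A model without those factors still computes its standard error as if that variation were present. If the factors predict outcome, the standard error is too large for the design, the test rejects too rarely under the null, and power is lost.

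How prognostic the factors are is not stated. Baseline self-harm and baseline borderline severity are plausible strong predictors of self-harm at week 12, and they were presumably chosen for balancing for that reason.

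The stake is efficiency in a small trial. The plan expects 70 × 0.7 = 49 patients with data, against 2 × 23 = 46 required, so there is little slack.

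**Working it through.** **1. The plan's own figure.** With 60% against 20%, pooled proportion 0.4, two-sided α 0.05, power 0.80 and no continuity correction:

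n = [1.96·√(2·0.4·0.6) + 0.8416·√(0.6·0.4 + 0.2·0.8)]² / 0.4² = (1.358 + 0.532)² / 0.16 = 22.3, so 23 per arm. This matches.

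Drop-out: 46/0.7 = 65.7, so 66; randomising about 70 covers it. Power of this week-12 comparison is 81% at 23 per arm, 84% at 24.5 per arm (49 completers) and 94% at 35 per arm.

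**2. Effect of leaving the factors out.** From the article: three minimisation factors and the 80/20 biased coin. Assumed: each factor binary and present in half of patients; log odds ratios for the week-12 outcome of (1, 1, 0.5) or (1, 2, 0.5); control intercept 0.4; conditional log odds ratio for arm of 1.8. For comparison, 60% against 20% is ln(1.5) − ln(0.25) = 1.79. Each scenario had 2,000 simulated trials, analysed as a single week-12 outcome by likelihood-ratio test.

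| N | Strengths | Type I error, unadjusted / adjusted | Power, unadjusted / adjusted |
|---|---|---|---|
| 49 | 1, 1, 0.5 | 3.0% / 6.4% | 76.8% / 82.6% |
| 49 | 1, 2, 0.5 | 2.9% / 7.2% | 65.0% / 79.1% |
| 70 | 1, 1, 0.5 | 3.8% / 5.6% | 91.1% / 93.8% |
| 70 | 1, 2, 0.5 | 3.5% / 6.7% | 84.5% / 90.5% |

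The Monte Carlo standard error of a 3% rejection rate is √(0.03 × 0.97/2000), about 0.4 points.

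**3. How to read the power column.** The two figures in a row come from the same data, so the comparison within a row is fair. The unadjusted figures should not be set against the planned 0.80. A conditional log odds ratio of 1.8 gives a marginal gap below 40 points. Averaging the outcome probability over the eight factor combinations gives 58.7% against 22.2% (gap 36.5 points) for the first set of strengths, and 57.6% against 25.1% (gap 32.5 points) for the second. The formula in step 1, solved for power at these rates and 24.5 per arm, gives 76% and 65%, almost exactly the simulated unadjusted values. Their distance below 0.80 therefore comes from the smaller gap. At the plan's own 40-point gap the unadjusted comparison keeps 84%.

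**4. Room for covariates.** Expected week-12 events among 49 completers: 24.5 × 0.2 + 24.5 × 0.6 = 19.6, about 20. That is few for arm plus several covariates, and fits with the adjusted tests running at 5.6–7.2%.

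**5. Linear mixed models.** If the effect is read as a difference in change from baseline, with baseline means left free, its variance relative to baseline adjustment is 2(1 − r)/(1 − r²) = 2/(1 + r). At an assumed correlation of r = 0.5 this is 1.33, or 33% more variance. The article does not say that the effect will be read this way.

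**The case against.** **The article condenses a fuller protocol, and covariates are often left to the analysis plan.** This would answer a silence, but the article lists the terms of both models. The point is about that list. By contrast, the coding of time and the choice of contrast are not stated, and such detail may well stand elsewhere.

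**The error is on the safe side.** This stands. Omitting the factors causes neither false positives nor bias. With 70 patients the unadjusted power was 85–91% even at the reduced gaps simulated.

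**Adjustment has its own cost.** This stands too: about 20 events, and adjusted tests above 5%. Part of the apparent gain is inflation.

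**Stronger readings that a reader might infer, and why they fail:**

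- *The primary test is the time-by-arm interaction, so the powered week-12 difference is not tested.* The section names the week-12 proportion as what is to be estimated and never makes the interaction the primary test. With categorical time, the three terms contain the week-12 arm difference. An interaction test would have lower power (49–63% for baseline to week 12 at 24 per arm, against 83–84% for the week-12 contrast, with baseline prevalence and correlation assumed), but the article does not specify that test.
- *Baseline is near separation because everyone is positive by eligibility.* Inclusion criterion 5 is met by recent parasuicidal behaviour and/or a BPDSI above 30, so baseline behaviour need not be universal.
- *Baseline status is absent from the model.* Pretreatment is one of the five measurements under Study design and may enter as a response. What the list lacks is baseline as a covariate.
- *The logistic estimate loses precision.* Adjusting a logistic model gives a conditional odds ratio and does not shrink its standard error. The loss is one of power.

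**Conclusion.** The point holds as an inefficiency in a stated model. The minimisation factors are missing from both lists of terms. Under the assumed strengths, the unadjusted week-12 test runs at about 3–4% instead of 5% and gives up about 6 to 14 points of power at 49 patients and 3 to 6 points at 70. The true gain from adjustment is smaller than these differences, because the adjusted tests ran above 5%.

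The figures rest on assumed covariate strengths and prevalences, on one visit instead of the full longitudinal model, and on treating the 49 as if all had been allocated by minimisation with none lost afterwards. The direction is secure if the factors are prognostic; the size is not. If they predict nothing, little is lost.

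A reader might infer that omitting the factors leaves the trial short of its planned 0.80. The figures do not show that: at a 40-point gap the formula still gives 84% with 49 completers. This is a worthwhile improvement, not a defect that invalidates the primary analysis.

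**What to change.** 1. **Primary model.** Add the minimisation factors as covariates and keep the model small. Baseline LPC can serve both as minimisation factor and as the measure of baseline behaviour, so no further baseline term is needed. Use a penalised (Firth-type) or small-sample-corrected fit.
2. **Linear mixed models.** Adjust for the same factors and for the baseline value of each outcome, with the post-baseline visits as responses.
3. **Clarification.** State that time is categorical and that the arm difference at week 12 is the primary test, in line with the Sample size section. Weeks 24, 36 and 52 are then secondary contrasts for retention. This corrects nothing in the listed terms.

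**Cost.** A few sentences. BPDSI and LPC are assessed before randomisation, and age is needed for eligibility and allocation, so no new data are required. The price is a few more parameters in a small sample and a conditional instead of a marginal odds ratio; reporting the week-12 proportions by arm alongside it keeps the result readable against 20% and 60%.
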